### Outcomes

Primary, secondary and safety outcomes are described and defined in table 1.

### Sample size

We intend to include 252 patients in Phase II/Stage 1 (189 in the active groups and 63 in the PbO group) and 189 patients in Phase II/Stage 2 (126 in the active groups and 63 in the PbO group). For Phase III, 564 additional participants will be randomized (376 in the active group and 188 in the PbO group). Thus, at the end of Phase III, 314 patients will have been evaluated in the PbO group and between 439 and 502 patients will have been evaluated in the treatment group if the study persists through the three phases. More details about the sample size calculation are described in Supplementary material 2 (Statistical Analysis Plan).

### Recruitment and patient retention

Recruitment will be granted for every patient hospitalized with COVID-19, who will be screened for eligibility criteria, sign the Informed Consent Form and be followed by a local study team who have been properly trained until discharge. Loss to follow-up is not expected in this period. If hospital discharge occurs before 15 days after the randomization date, these patients will be evaluated by telephone call, which will be performed by the center 15 days after randomization and 28 days later. Those who return home before D10 will be assessed daily until completion of the study drug treatment period (10 days) by telephone call or in person on D3, 6 or 10 to collect nasal swabs and to assess treatment compliance.

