### Blinding

This study is not a global double-blind study in Stages 1 and 2, as we have 3 drugs with different physical characteristics, rendering global blinding impossible. Both the participant and investigator can know, after randomization, to which drug group the patient was allocated. However, none will know whether the capsule or coated tablet to be administered contained the active drug or PbO, ensuring blinding of participants and investigators within that specific group, as well as the outcome assessors.

In Phase 3, the global blinding of the stage is possible, since we will have only one active group and a PbO.

A partnership will be established with a handling pharmacy duly licensed to carry out the fractioning, repacking, labeling and blinding process of the drugs. The pharmacy will deliver all the drugs to a logistic contractor, who will deliver them to the centers.

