#### Retention

Data will be collected from patients admitted to the ICU/hospital, which reduces the risk of data loss due to loss of follow-up. Telephone contact will be made centrally by professionals who have not participated in other stages of the study.

- **Postdischarge follow-up:** Patients discharged less than 15 days after randomization will be contacted by telephone daily until D10 and on D15 and 28 and questioned using a structured form by an interviewer who is blinded to the research participant’s allocation group. In this contact, the participant or his or her family member will be asked about the observation of adverse events, and ordinal scales of 6 and 7 points will be applied for the secondary outcomes.

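### The article assigns the post-discharge outcome calls both to the site and to blinded central interviewers; the two sections need to be reconciled (minor)

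*Protocol article*

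**What the plan says.** All references are to the protocol article.

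- **Recruitment and patient retention.** Patients are to "be followed by a local study team who have been properly trained until discharge". Those who leave hospital before day 15 are then "evaluated by telephone call, which will be performed by the center 15 days after randomization and 28 days later".
- **Retention.** For the same patients, "Telephone contact will be made centrally by professionals who have not participated in other stages of the study". Under post-discharge follow-up they "will be contacted by telephone daily until D10 and on D15 and 28", and are "questioned using a structured form by an interviewer who is blinded to the research participant’s allocation group". In these contacts adverse events are asked about, and "ordinal scales of 6 and 7 points will be applied for the secondary outcomes".
- **Blinding.** In Stages 1 and 2, "Both the participant and investigator can know, after randomization, to which drug group the patient was allocated". Active drug versus placebo stays concealed within a drug group, for outcome assessors too. Global blinding is described as possible in Phase III.
- **Statistical methods.** The placebos for the different drugs are always analysed as one group.
- **Table 1.** Levels 1 and 2 of the seven-level day-15 scale both mean out of hospital. They differ only in whether normal activities have been resumed.

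**The concern.** The same contact is given to two different callers. One belongs to the site, where the drug group can be known during Phase II. The other is a blinded interviewer with no other part in the study. A site team following the first section would replace the safeguard in the second.

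This matters more here than in a trial with a matched placebo for each comparison. Concealing active drug from placebo within a drug group protects a comparison made within that group. The planned comparison sets one drug against placebo patients from all drug groups, most of whom are visibly in another group. A caller who knows the group, and expects more of one drug than of another, could score the two sides of that comparison differently.

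The exposed items are those that depend on judgement or prompting by telephone: level 1 versus level 2 on the secondary day-15 scale, and adverse events. Serious adverse events also enter the criteria for discontinuing an arm for safety, so neutral reporting of them has some weight.

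**Working it through.** **1. Who is meant by the center.** The article uses the word for the participating site when it describes stratified randomization, the pharmacy of each center and the random effect in the Phase III model. The coordinating body is named separately, as the Coordinating Center, under Drug accountability. The sentence on calls also follows directly on the local study team. The natural reading is the site, and it conflicts with the Retention section.

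**2. What knowledge of the drug group reveals in Phase II/1.** The inputs are 252 patients (Sample size) and allocation 3:3:3:1:1:1 (Phase II/1 analysis).

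- One allocation unit: 252 / 12 = 21.
- Each active arm: 3 × 21 = 63. Each placebo arm: 21. Pooled placebo: 3 × 21 = 63.
- Share of active patients within any visible drug group: 63 / 84 = 75%, the same in all three groups.
- For a given drug, all 63 active patients are in its visible group. Only 21 of the 63 pooled placebo patients are, and 42 are visibly elsewhere.

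Knowing the group says nothing about active versus placebo within it, but it does separate the two sides of the pooled comparison.

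**3. Illustrative size in Phase II/1.** The article gives no day-15 distribution, so I assume 35/35/5/8/3/6/8% over levels 1 to 7 in every arm, meaning a drug with no effect. I also assume that callers move 5 or 10 percentage points from level 2 to level 1 for everyone in the tested drug's visible group. The caller cannot tell active from placebo there, so the 21 same-group placebo patients shift too. Pooled placebo then moves by 21/63, one third, of the shift. I fitted a proportional-odds model to the expected counts, with an odds ratio below 1 favouring the drug.

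| Shift in drug group | Level 1 / level 2, active | Level 1 / level 2, pooled placebo | Odds ratio | Log OR / SE |
|---|---|---|---|---|
| 5 points | 40 / 30% | 36.7 / 33.3% | 0.93 | 0.077 / 0.324 = 0.24 |
| 10 points | 45 / 25% | 38.3 / 31.7% | 0.86 | 0.155 / 0.325 = 0.48 |

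The last column shows absolute values.

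**4. The same shift in the pooled Phase III data.** Take 439 active and 314 placebo patients (Sample size), with only the Phase II/1 patients of that drug group affected.

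- 5 points: active moves 5 × 63/439 = 0.72 points and placebo 5 × 21/314 = 0.33 points. The odds ratio is 0.99, or 0.07 SE.
- 10 points: 1.44 and 0.67 points. The odds ratio is 0.98, or 0.13 SE.

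**5. The call days.** Read literally, the second call in the first section falls on day 15 + 28 = 43. The Retention section says D28, Table 5 has no column after D28, and the late outcomes in Table 1 stop at 28 days.

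**The case against.** The strongest reply is that the safeguard is already written down. The Retention section is the operational text: it names the form, the scales, the days and the blinded interviewer. The other section is a short summary that mentions neither scoring nor blinding. The center might also be read as the coordinating center. And this is a condensed article, so the full protocol may settle the matter.

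Part of this stands. The intention is probably the one in the Retention section. But the article itself gives two callers for one contact, and its own usage points to the site, so the text still needs correcting.

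It is also fair to say that little is exposed. The level 1 versus level 2 judgement exists on one secondary scale; the six-level day-7 scale has a single level for patients out of hospital. Viral-load slope comes from swabs, and mortality and discharge are objective. A bias needs callers who favour one repurposed antiviral over another, and nothing in the article suggests that they do. Participants may know their own drug group, which no choice of caller can cure.

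Three stronger readings are tempting and unsupported:

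- A reader might infer that only the active arm would be scored more kindly, which gives odds ratios of 0.89 and 0.79. The Blinding section rules this out, because the caller cannot separate active from placebo within the group.
- A reader might carry the full shift into the 439 versus 314 comparison. Phase III can be globally blinded, so only patients from the earlier stages could be affected.
- A reader might conclude that the D28 contact is lost to a day-43 call. Given Tables 1 and 5 and the Retention section, the phrase is almost certainly loose wording for D28.

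**Conclusion.** The contradiction over who makes the calls is real on the natural reading, and it is minor. If sites made the calls in Phase II, drug-group knowledge could reach a comparison that within-group blinding does not protect. The effect would be confined to the secondary day-15 scale and to adverse events reported by telephone. No error in the Phase II primary outcome follows.

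The possible bias is 0.24 to 0.48 standard errors in Phase II/1 and about 0.07 to 0.13 in the pooled Phase III data. These figures rest on an assumed distribution and an assumed shift. They show scale and are not estimates. The effect on adverse events cannot be sized from the article. The timing phrase is a wording slip to tidy in the same edit.

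**What to change.** Amend Recruitment and patient retention to match Retention. The D15 and D28 calls, both counted from randomization, should be made centrally by interviewers who are blinded to allocation, including drug group, and take no other part in the study. Site staff keep the in-person visits up to D10 for swabs and drug accountability. Counting both days from randomization also removes the loose timing phrase.

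Since the article reports 256 patients already randomized, the sponsor should also state which procedure the sites followed.

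The cost is wording only, because the central blinded interviewers are already planned.

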### Sequence allocation

The randomization list will be generated electronically using appropriate software. Randomization will be performed in blocks and stratified by center. In Phase II Stage 1, the blocks will have 12 codes (positions), with each treatment group represented by three different codes and each PbO by a single code. In Phase II, Stage 2, the blocks will have six codes, the treatment groups will be represented by two different codes, and each PbO will be represented by a single code. Block sizes will be adapted if any arm is discontinued. In the third stage of the study, the blocks will have six codes, four codes representing the treatment group and 2 codes representing the PbO group.

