### Objectives

The main objective of the REVOLUTIOn trial is to evaluate whether repurposed antiviral drugs alone or in combination are effective at decreasing the viral load and increasing the number of days free of respiratory support. The primary and secondary objectives are described in table 1.

**Table 1 t1:** Objectives and outcomes

Primary objective	Outcome/primary variables
Phase II first stage (II/1): compare the effect of treatment with single antivirals against placebo in reducing the load of SARS-CoV-2 in nasopharyngeal swab samples	Decay rate (slope) of the SARS-CoV-2 viral load logarithm in nasopharyngeal and swab samples evaluated at D0, D3, D6 and D10 after randomization
Phase II second stage (II/2): compare the effect of treatment with combinations of antivirals compared to isolated ones in reducing the SARS-CoV-2 viral load in nasopharyngeal swab samples	Decay rate (slope) of the SARS-CoV-2 viral load logarithm in nasopharyngeal and swab samples evaluated at D0, D3, D6 and D10 after randomization
Phase III: compare the efficacy of antivirals alone or in combination to the placebo in increasing the number of days free of respiratory support	Days free of respiratory support, defined as the number of days without oxygen, noninvasive ventilation/high-flow nasal cannula or the need for mechanical ventilation within 15 days from randomization 1. This parameter is counted as follows: D = zero (if the patient dies within 15 days (either in the hospital or at home or remains on respiratory support with oxygen through a nasal catheter, noninvasive ventilation, high-flow nasal catheter, or mechanical ventilation ≥ 15 days) D = 15 - x (if the patient is released from the hospital in < 15 days, where x represents the number of days with respiratory support during hospitalization)
Secondary objectives	Outcomes/secondary variables
Evaluate the status using the 7-stage ordinal scale for clinical outcomes on D15	Percentage of patients in various stages: 1. Not hospitalized with resumption of normal activities 2. Not hospitalized, but unable to resume normal activities 3. Hospitalized, with no need for supplemental oxygen 4. Hospitalized, requiring supplemental oxygen 5. Hospitalized, requiring high-flow nasal oxygen therapy, noninvasive mechanical ventilation, or both 6. Hospitalized, requiring blood oxygenation through a membrane system, invasive mechanical ventilation or both 7. Death

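### One fixed, published block size per stage within centre, with the drug group visible after allocation, lets higher-recruiting sites predict drug-group allocation in Stages II/1 and II/2

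*Protocol article*

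**What the plan says.** Under Sequence allocation the protocol article states "Randomization will be performed in blocks and stratified by center". For the first stage it gives "In Phase II Stage 1, the blocks will have 12 codes (positions), with each treatment group represented by three different codes and each PbO by" one code. For the second it gives "In Phase II, Stage 2, the blocks will have six codes, the treatment groups will be represented by two different codes", with one code for each placebo. The only variation it allows is "Block sizes will be adapted if any arm is discontinued"; it mentions no random variation of size.

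The Blinding section says of Stages 1 and 2: "Both the participant and investigator can know, after randomization, to which drug group the patient was allocated". What remains masked is narrower: "none will know whether the capsule or coated tablet to be administered contained the active drug or PbO". The Interventions section gives the single and the combination arm of II/2 their own placebos, so single versus combination is visible to the site.

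Allocation concealment rests on a central web-based system. Table 1 states the II/2 objective as to "compare the effect of treatment with combinations of antivirals compared to isolated ones in reducing the SARS-CoV-2 viral load". Statistical methods pools all placebos into one control group. The Discussion says the article matches the protocol approved by the national and local ethics committees.

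**The concern.** A central system hides the list, but it cannot stop a site from counting its own past allocations against a known block composition. In drug-group terms each II/1 block holds 4 ATV, 4 DCV and 4 SOF/DCV places (3 active and 1 placebo each), and each II/2 block holds 3 single and 3 combination places (2 active and 1 placebo each). Once most of a block is used, the remaining places are partly or wholly known.

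An investigator who can anticipate the next drug group could bring forward or hold back a particular patient. Masking active against placebo protects only comparisons inside one drug group, and the planned comparisons cross groups. In II/2 the contrast named in Table 1, combination against single, is exactly the visible one. In II/1 each active arm is tested against a placebo group of which two thirds comes from the other two drug groups, and the ranking of decay rates that decides which regimen advances is also made across groups. A laboratory endpoint does not remove the problem, because selection of this kind acts at enrolment and not at assessment.

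**Working it through.** **The plan's own figures reproduce.** II/1: 3×3 + 3×1 = 12 codes; 252 × 9/12 = 189 active and 252 × 3/12 = 63 placebo. II/2: 2×2 + 2×1 = 6 codes; 189 × 4/6 = 126 active (63 per arm) and 189 × 2/6 = 63 placebo. These match Sample size.

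**Predictability in full II/2 blocks (visible groups 3 + 3).**
- Position 4 is certain if the first three were all one group: 2/20 = 10%.
- Position 5 is certain if the last two belong to one group: 2 × (3/6 × 2/5) = 40%.
- Position 6 is always certain.
- Certain in total: 0.10 + 0.40 + 1.00 = 1.5 of 6, or 25.0%.
- Guessing the group with most places left is right at positions 1 to 6 with probability 0.5, 0.6, 0.6, 0.7, 0.7 and 1.0. The sum is 4.1, and 4.1/6 = 68.3%, against 50% by chance.

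**Predictability in full II/1 blocks (4 + 4 + 4).**
- Position 9 is certain in 3 × (4·3·2·1)/(12·11·10·9) = 0.6% of blocks.
- Position 10 is certain in 3 × (4·3·2)/(12·11·10) = 5.5%.
- Position 11 is certain in 3 × (4/12 × 3/11) = 27.3%.
- Position 12 is always certain.
- Certain in total: 1.33 of 12, or 11.1%.
- Exact enumeration of best guessing gives 6.144 correct of 12, or 51.2%, against 33.3% by chance.

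**At the average centre.** Study settings gives about 60 hospitals, so 252/60 = 4.2 patients per centre in II/1 and 189/60 = 3.15 in II/2. Over the first 4 positions of a II/1 block nothing is certain and guessing is right 37.7% of the time. Over the first 3 positions of a II/2 block nothing is certain and the rate is (0.5 + 0.6 + 0.6)/3 = 56.7%. Over the first 4 it is 60.0%, with the fourth certain in 10% of blocks.

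**What it could do to the II/2 contrast.** Assumption, not in the documents: every investigator shifts the prognosis of the enrolled patient by +d or −d SD according to the guessed group, and does not steer when the groups are tied. With guess rate g, the spurious combination-minus-single difference is 2(2g − 1)d. With 63 per arm the standard error is √(2/63) = 0.178 SD. The rejection rate of a two-sided 5% test with no true effect, at d = 0.2, is:
- First 3 patients per centre: 2 × 0.133 × 0.2 = 0.053 SD, rejection 6.0%.
- First 4 patients per centre: 2 × 0.200 × 0.2 = 0.080 SD, rejection 7.3%.
- Every block full: 2 × 0.367 × 0.2 = 0.147 SD, rejection 13.0% (7.0% at d = 0.1 and 23% at d = 0.3).

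Against pooled placebo in II/2, half the controls share the active arm's drug group, so the bias halves. At d = 0.2 rejection is 7.0% with full blocks and 5.3% with three patients per centre.

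**What varying the size would gain.** A fixed II/2 block of 12 would still leave 14.3% certain and 64.3% guessed. If sizes 6 and 12 are drawn with equal probability and the end of a block is not disclosed, the same enumeration, weighting each possible block by its probability given the allocations seen so far, gives a best-guess rate of about 65% against 68.3%. A site can no longer be certain of its sixth patient, because the block may be one of 12.

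**The case against.** The case for leaving this alone is substantial, and much of it stands.

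- A reader might infer that sites can routinely work out the next drug group. The documents do not support that. Certainty comes only late in a filled block, the average load is far short of a full block, and how recruitment spreads over centres is not given.
- A reader might take 13% as the size of the problem. It needs full blocks at every centre, a log and optimal guessing everywhere, and uniform steering of 0.2 SD, a value with no source in the documents. It also applies only to combination versus single. Table 1 names that contrast, but the Phase II/2 text says the same statistic as in II/1 will be used, which is treatment against control. There the effect is smaller.
- A reader might infer that active versus placebo is revealed, or that steering took place. Neither follows: within-group masking is intact, and nothing in the article shows selective enrolment.
- Current status reports 256 patients randomized against 252 planned for II/1, so the II/1 list can no longer change. II/2 runs only if ATV and a DCV presentation both prove effective and safe.
- The gain in guess rate from varying blocks is modest.

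What does not stand is that the central system settles the matter. It protects the list, not the inference from a known composition and visible past allocations. Nor is this a detail left to the analysis plan, since the article itself states the scheme.

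**Conclusion.** The weakness is real and limited. One fixed, published block size per stage within centre, combined with a visible drug group, makes late allocations in a block predictable: 25% certain and 68% guessable in full II/2 blocks, 11% and 51% in full II/1 blocks. At the average load nothing is certain and guessing is right about 57% (II/2) and 38% (II/1) of the time. The exposure is therefore confined to higher-recruiting centres, whose number the article does not give.

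The comparisons exposed are those across drug groups: combination versus single in II/2, and the arm ranking and the pooled-placebo comparison in II/1. If steering of 0.2 SD occurred, the false-positive rate of a 5% combination-versus-single test would be about 6-7% at the average load and at most 13%. Phase III allocation is globally blinded and does not share the weakness. This is a cheap improvement to make before II/2, not a flaw that invalidates the design.

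**What to change.** If II/2 is run, generate its list in the existing central system with randomly varying block sizes that keep 2:2:1:1, for example 6 and 12. In the protocol, say only that block sizes vary and are not disclosed to sites, and keep the sizes in a restricted randomization document.

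The cost is one regenerated list and one changed sentence. The downside is slightly looser balance within centre. The benefit is that end-of-block certainty largely disappears, with a modest fall in guessing from 68% to about 65%.

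For II/1 the only step left is to check baseline balance by drug group and centre, with attention to the centres that filled or nearly filled a block.

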### Allocation concealment

The concealment of the randomization list will be maintained through a centralized, automated, internetbased randomization system, available 24 hours a day, developed by a team of programmers and researchers from the Research Institute of *HCor-Hospital do Coração* (HCor).

